## Abstract

**Background:**

Russia is one of the very few industrialised countries in the world where life expectancy has been declining. Alcohol has been implicated as a major contributor to the rapid fluctuations observed in male life expectancy since 1985 that have been particularly marked among working-age men.

One approach to reducing the alcohol problem in Russia is 'brief interventions' which seek to change views of the personal acceptability of excessive drinking and to encourage self-directed behaviour change. There is limited understanding in Russia of the salience and applicability of Motivational Interviewing (MI), a well-defined brief intervention commonly used to target alcohol-related behaviour, but MI may have important potential for success within the Russian context.

**Methods/Design:**

The study will be an individually randomised two-armed parallel group exploratory trial. The primary hypothesis is that a brief adaptation of MI will be effective in reducing self-reported hazardous drinking at 3 months. The secondary hypothesis is that it will be effective in reducing self-reported past week beverage alcohol consumption, alcohol dependence and related problems at 3 months and at 12 months. MI will also be effective at 12 months in reducing self-reported hazardous drinking, alcohol dependence and related problems, proxy reported hazardous drinking, and recent alcohol use as indicated by bio-markers.

Participants are drawn from the Izhevsk Family Study II, with eligibility determined based on proxy reports of hazardous drinking in the past year. All participants undergo a health check, with MI subsequently delivered to those in the intervention arm. Signed consent is obtained from those in the intervention arm at this point. Both groups are then invited for 3 and 12 month follow ups. The control group will not receive any additional intervention.

**Trial Registration:**

ISRCTN82405938

## Background

### What is the problem?

Russia is one of the very few industrialised countries in the world where life expectancy has been declining [1]. Analysis of routinely collected data over the past few decades has implicated alcohol as a major contributor to the rapid fluctuations observed in male life expectancy since 1985, that have been particularly marked among working-age men. For example, there was an increase in life expectancy following the start of the anti-alcohol campaign in 1985 [2] that led to falls in levels of per capita alcohol consumption in Russia [3-5] Rates of mortality from alcohol-related deaths among working age men decreased particularly sharply [5]. However, with the collapse of the Soviet Union this progress was reversed with a 6-year decline in male life expectancy between 1990 and 1994 that coincided with increases in per capita alcohol consumption. There is growing evidence linking excessive alcohol consumption to the high mortality among working age men in Russia [6,7]. A recent study demonstrated the large role played by alcohol, and in particular, of hazardous drinking patterns including a phenomenon termed "zapoi" (episodes of extended periods of drunkenness during which the participant withdraws from normal life), and consumption of surrogate alcohols (alcoholic substances not intended to be drunk, also known as non-beverage alcohols) in deaths from all causes and alcohol-related causes among men of working age in Russia [7].

### What is the evidence so far about what works to reduce alcohol problems?

One important approach to reducing the alcohol problem in Russia would be through government action to control manufacture and sale of drinkable surrogates and limit the availability and increase in price of legitimate alcoholic beverages. However there is also an urgent need to develop individual-level treatment services that are effective in the Russian context, where there has been little or no employment of individual counselling. There is an additional need to reach beyond specialist treatment services, as the majority of hazardous and harmful drinkers elsewhere do not access such provisions.

Another approach that may be appropriate is that of 'brief' interventions. These seek to change views of the personal acceptability of excessive drinking and to encourage self-directed behaviour change. They include both simple forms of advice and brief counselling techniques. Widespread dissemination of these interventions is possible as they can be delivered by a wide range of generic rather than specialist practitioners. These techniques have been shown to be effective in many other contexts. An international evidence-base has accumulated over more than 20 years, with efficacy data originating mainly, but not exclusively, from English language speaking countries. Reductions in volume of alcohol consumed are typically about 20–25% [8] and reductions in the proportions of hazardous drinkers are between 10–19% [9] The number needed to treat is about 8 for both hazardous alcohol consumption and for alcohol-related harm [9]. Reductions in alcohol problems of a similar magnitude and in health service utilisation have also been identified [10].

Motivational Interviewing (MI), a well-defined intervention [11], has been increasingly prominent within this literature in more recent years. One systematic review identifies 31 trials of MI, with alcohol being the most commonly targeted behaviour [12]. MI has been defined as "a facilitative, patient-centred counselling style for helping people explore and resolve ambivalence [11]." Brief adaptations of this counselling style offer promising potential to optimise the effectiveness of brief interventions. However, very little is known about the salience and applicability of these interventions in Russia – a country with a distinctive pattern of heavy drinking.

### Aims of the study

The study is a trial to explore the efficacy and acceptability of a brief intervention aimed at reducing the prevalence of hazardous drinking in working age men in a typical Russian city (Izhevsk). This will prepare the ground for subsequent effectiveness evaluations in a range of routine service settings with different populations of hazardous drinkers. Experience conducting this trial will provide an indication of the extent of possible benefit specifically within Russia. In addition, dissemination of information about the trial and its results is expected to contribute directly to improving understanding (locally, nationally and internationally) of the nature of this major problem in Russia and the required responses.

## Methods/Design

The study will be an individually randomised two-armed parallel group exploratory trial.

### Hypotheses

#### Primary hypothesis

A brief adaptation of MI will be effective in reducing self-reported hazardous drinking at 3 months.

#### Secondary hypotheses

MI will be effective in reducing self-reported past week beverage alcohol consumption, alcohol dependence and related problems at 3 months and at 12 months. MI will also be effective at 12 months in reducing self-reported hazardous drinking, alcohol dependence and related problems, proxy reported hazardous drinking, and recent alcohol use as indicated by bio-markers.

### Trial inclusion criteria

The men recruited into the trial will be drawn from a longitudinal observational study that is part of the Izhevsk Family Study II. This is based on 1750 men who were the controls in a case-control study of premature mortality conducted 2003–5 [7] supplemented by a further 250 men recruited using an identical protocol over a two month period in 2006. At initial recruitment to the case-control study, the men were aged 25–54 years and resident in Izhevsk. Interviews were conducted with 1750 control proxies, and 1691 of the controls themselves. For the supplementary group of 250 men, interviews were again carried out with proxies and with the men themselves. Interviewer-administered, structured questionnaires were used to gather information on a wide range of behaviours and characteristics, including alcohol consumption, tobacco use, a range of socio-economic and demographic factors, health status, and health-related behaviours.

Over an 18 month period (2007–8) as part of the longitudinal study we will attempt to recontact all of the 2000 men previously interviewed who are still alive and living in Izhevsk. Participants, who will be aged between 27 and 59 years of age, will be asked to take part in a re-interview study involving themselves as well as a proxy informant. Those who take part in this stage will then be invited to have a physical examination (referred to as a "Health Check") a few weeks later, to be carried out by a one of 4 specially trained doctors either in their own home or at a polyclinic in the city, according to the participant's preference.

Eligibility for entry to the trial will be determined according to information gathered at the initial re-interviews with proxy informants who live in the same households as the participants. These criteria are specified in Table 1. Men who had a proxy in the last study but now live alone, or for whom no proxy interview can be obtained, will be recruited on the basis of self reports of the same measures and using the same cut-offs.

**Table 1 T1:** Eligibility and outcome definitions

Eligibility/Outcome	Criteria
Eligibility criteria for trial entry based on re-contact interview	*PROXY *reports (or self reports for men living alone) of hazardous drinking defined as one or more occurrences of any of the following: • zapoi in the past year • surrogates in the past year • hangover and/or excessive drunkenness and/or going to sleep clothed due to being drunk twice or more per week on average over the past year • weekly average of 250 mls or more of ethanol from beverages over the past year (ie 25+ UK alcohol units/week)

Primary outcome (3 months post-randomisation)	*SELF *report of hazardous drinking in defined as one or more occurrences of any of the following: • zapoi in the past month • surrogates in the past month • hangover and/or excessive drunkenness and/or going to sleep clothed due to being drunk twice or more per week on average over the past year • 250 mls or more of ethanol from beverages in the past week from beverages (ie 25+ UK alcohol units)

Secondary outcome (12 months post-randomisation)	*SELF *report of hazardous drinking defined as one or more occurrences of: • *as above at 3 months*

Supplementary secondary outcome (12 months post-randomisation)	*PROXY *report of hazardous drinking defined as one or more occurrences of: • *as above at 3 months except proxy rather than self- report* *SELF *completed: • AUDIT questionnaire (W.H.O. developed global screening assessment of hazardous drinking [26] • Leeds Dependency questionnaire [27] • SIP (Short Index of Problems) questionnaire [28] Biomarkers of: • liver damage (GGT, ALT, AST) • recent heavy drinking (CDT) [29]

### Trial exclusion criteria

Refusal to have a baseline health check and/or refusal to be followed up at 3 and 12 months will result in exclusion from the trial.

### Randomisation and consent

Although in most trials, consent to random allocation is sought before the allocation takes place, there are some acceptable exceptions when randomisation is carried out prior to consent (Zelen randomisation), as in this trial (see Ethics, below).

Data collected at the baseline interview will be sent to the randomisation service in London, allowing participants to be allocated to intervention or control prior to their health check appointment. Minimisation criteria (including age, surrogate use in past year, and living alone status) will be used to ensure a reasonable balance with respect to the principal known confounding factors.

Signed consent for taking part in the active arm of the trial will be obtained at the end of the health check. This is the last of a sequence of consents that the participant will need to give in the course of recontact as outlined in Table 2. Consent will be obtained differently for the intervention and control groups:

**Table 2 T2:** Consent

What	When	Who obtains consent?	Comments
Oral consent for interview	Baseline recontact interview	Interviewer	Recorded by interviewer in questionnaire

Oral consent to be recontacted in future to assist with research (not-specific)	Baseline recontact interview	Interviewer	Recorded by interviewer in questionnaire

Expression of interest in health check following brief description of health check- copy of which to be left with participants	Baseline recontact interview	Interviewer	NOT consent per se, but indication of whether interested in taking part and if so, contact details (telephone number)

Signed consent for health check procedures	Health check	Doctor	Participants given information on BP and anthropometry and questionnaire, and blood taking

Signed consent to take part in active intervention arm of MI trial	Health check	Doctor	For subset of participants who are eligible, randomized to intervention arm of trial, and turn up for health check. Note, no explicit consent for being in control arm, beyond oral recontact agreement

a) Intervention group: Consent will be sought at the time of the health check by medical personnel involved. They will be trained to explain the purpose of the trial, provide written information and answer "frequently asked questions" about the trial. The consent being requested is (i) to take part in the intervention and (ii) to provide follow up data in 3 and 12 months time for the longitudinal study (even if they are not willing to take part in the intervention);

b) Control group: Consent to take part in the trial will not be sought from men randomised into the control group as they need to remain unaware of the trial (see Ethics, below). However, they will have previously given general consent to be followed up at the time of the initial re-interview.

### Interventions

#### a) Treatment group

MI will be delivered following completion of the health check (part of the longitudinal study protocol). An adaptation of MI has been developed for the Russian context, and includes topics such as surrogate drinking and zapoi. MI involves empathic questioning and listening, with a view to the development of discrepancy between alcohol use and other goals and values and the eliciting of personalised statements about change. The full intervention comprises up to four sessions. These will be delivered at home or in a clinic by specially trained practitioners with the two core sessions being approximately two weeks apart, with additional sessions (up to a maximum of 2) being available upon request. Practitioners have been trained and supervised in Russian, with a period of practice-based learning following an introductory workshop. Approximately 10% of sessions will be audio-recorded for quality control and supervision purposes.

#### b) Control group

This group will not receive any intervention other than having a health check as part of the longitudinal study and being invited for 3 and 12 month follow ups.

### Outcome measures

Follow-up data collection for both groups will take place after 3 and 12 months

Outcome interviews at 3 and 12 months will be partly interviewer-administered, and partly self-completed by participants, in order to replicate the administering of the same tools at baseline. The primary and secondary outcomes at 3 and 12 months are summarised in Table 1.

### Recruitment rate

Assuming that the overall prevalence of hazardous drinking remains the same over time, we have estimated from the original Izhevsk Family study data that approximately 25% of the 2000 men initially invited to take part in the Izhevsk family study II will be eligible for inclusion in the trial. Assuming a 60% response rate from those invited to participate in the Izhevsk family study 2 we would expect to be able to identify 300 hazardous drinkers eligible for the trial.

### Sample size

Based on current MI literature it is expected that 25% of participants in the intervention arm will stop hazardous drinking, as those in the control arm will have had minimal contact with the study and will not have been specifically told they are involved in research relating to alcohol, spontaneous reduction in hazardous drinking of more than 5% is unlikely. We have selected a difference at approximately the upper limit of the projected effect size based on previous meta-analyses [8] as a result of this unusual characteristic of the study design. We are unaware that such a Zelen design (see later) has previously been used in any study of brief alcohol intervention. Power calculations are therefore based on detecting a 20% difference between randomised groups (from 95% to 75%) with 90% power at the 5% level of statistical significance. A sample of at least 130 men (65 in each arm) will therefore be required. As randomisation was carried out prior to consent to MI, we assume that 20% of the participants in the intervention arm will not agree to receive the intervention. We also assume that there will be a 20% loss to follow for the 3 month assessment in both trial arms. This requires inflating the sample size to between 200 and 250 participants.

It should be noted that one aim of this exploratory trial will be to assess the assumptions behind these calculations in order to design a definitive study with power to assess smaller differences which could have nonetheless have major public health benefits.

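### The 95% control rate behind the 90% power is not supported for the primary outcome as Table 1 defines it

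*Protocol article*

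**What the plan says.** The Sample size section plans for "detecting a 20% difference between randomised groups (from 95% to 75"%, "with 90% power at the 5% level of statistical significance", and arrives at 65 men per arm. On the intervention side, "it is expected that 25% of participants in the intervention arm will stop hazardous drinking". On the control side, "spontaneous reduction in hazardous drinking of more than 5% is unlikely"; the reason given is that controls have little contact with the study and are not told that it concerns alcohol. The section then allows for 20% of the intervention arm declining MI and 20% loss in both arms, giving 200 to 250 men. It describes the difference as about the "upper limit of the projected effect size based on previous meta-analyses [8"], and adds that the exploratory trial will itself test the assumptions behind the calculation.

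Table 1 defines entry and primary outcome separately. At entry the surrogate item reads "surrogates in the past year"; in the outcome it reads "surrogates in the past month". Zapoi changes window in the same way, and volume goes from a weekly average over a year to the past week. Entry uses a proxy's report, or self-report where the man lives alone or no proxy interview can be obtained. The outcome is self-report for everyone.

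**The concern.** The 95% is obtained by starting every control at 100% hazardous on entry and taking off 5% for genuine change. That works only if entry and outcome are the same measure, and for most men they are not. A man can enter on a single zapoi episode or a single use of surrogates in twelve months. If he drinks in exactly the same way afterwards, the relevant month may contain neither. His intake in one particular week may fall below a threshold that his yearly average exceeds. He may also report less than his proxy did. None of this is spontaneous reduction in drinking, yet each lowers the control proportion.

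For a given absolute difference, a comparison of two proportions has most power when one of them is close to 0 or 1, so 95% is a favourable planning value. If the true control rate is lower, a null result might be read as coming from a 90%-power trial when the power was less. The Data Monitoring Committee's remit to say whether a clear outcome is obtainable would be affected in the same way.

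**Working it through.** **Inputs from the Sample size section:** control 95%, intervention 75%, 5% significance (taken as two-sided, which reproduces the stated number), 90% power, 20% non-uptake in the intervention arm, 20% loss in both arms, 200 to 250 randomised.

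**Formula (pooled normal approximation, no continuity correction):** with p̄ = (p1 + p2)/2,

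n per arm = [1.96·√(2p̄(1−p̄)) + 1.2816·√(p1(1−p1) + p2(1−p2))]² / (p1 − p2)²

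power = Φ{[|p1 − p2|·√n − 1.96·√(2p̄(1−p̄))] / √(p1(1−p1) + p2(1−p2))}

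**1. The plan's own figure.** p1 = 0.95, p2 = 0.75, p̄ = 0.85: n = [1.96 × 0.505 + 1.2816 × 0.485]² / 0.04 = 64.9, so 65 per arm, with power 90.1%. The arithmetic is right; only the input is in question.

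**2. The plan's allowances.** If the 20% who decline MI behave like controls, the intention-to-treat difference is 0.8 × 20 = 16 points (95% v 79%). That needs 91 per arm; 182/0.8 = 227.5, which lies within 200 to 250. After 20% loss, 200 randomised leaves 80 per arm and 250 leaves 100.

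**3. Entry and outcome side by side (Table 1).**

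| Component | Entry window | Outcome window |
|---|---|---|
| Zapoi | year | month |
| Surrogates | year | month |
| Ethanol volume, 250 ml threshold | weekly average over a year | past week |
| Hangover, drunkenness, sleeping clothed | year | year |
| Informant | proxy (self for some) | self |

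Three of the four components shorten, and the informant changes for men entered on a proxy's report. Nothing in the document estimates how many men eligible on entry would meet the outcome definition on the same day.

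**4. Power at lower control rates.** The rates below 95% are assumptions. Each cell gives 80 to 100 evaluable per arm.

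| Control rate | 16-point difference held | Ratio 79/95 held |
|---|---|---|
| 95% | 86–93% | 86–93% |
| 90% | 75–84% | 72–81% |
| 85% | 67–77% | 59–69% |
| 80% | 62–72% | 49–58% |
| 70% | 55–65% | 34–41% |
| 60% | 53–62% | 25–30% |

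Example at 90% v 74% with 80 per arm: (0.16 × √80 − 1.96 × √(2 × 0.82 × 0.18)) / √(0.09 + 0.1924) = (1.431 − 1.065)/0.531 = 0.689, and Φ(0.689) = 75%.

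**5. Source of the difference.** The Sample size section cites reference [8]. The Background section cites [8] for reductions in volume (20–25%) and [9] for the proportion of hazardous drinkers (10–19%), adding "The number needed to treat is about 8 for both hazardous alcohol consumption and for alcohol-related harm". An NNT of 8 is 1/8 = 12.5 points. At 95% v 82.5% with 80 to 100 per arm, power is 71–80%.

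**The case against.** Several points on the other side stand.

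- The drunkenness item keeps its one-year window. At 3 months about nine of those twelve months precede randomisation, so the item tends to keep unchanged controls in the hazardous category.
- Men living alone or without a proxy interview enter on self-report, so their informant does not change.
- The outcome is met by any one of four components, so a man who entered on one may still qualify on another.
- The protocol calls the trial exploratory, says it will assess these assumptions, and openly chose an upper-limit effect because of the Zelen design.
- There is slack. With 100 per arm and an undiluted 20 points, power is still 95% at a 90% control rate and 91% at 85%, though this spends the allowance for non-uptake. If all 300 expected eligible men entered (150 × 0.8 = 120 per arm), 16 points would have 90% power at a 90% control rate, but 79% at 80%.

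A reader might go further and infer that the control rate must fall far below 95% and that the power is certainly not delivered. The document gives no rate for the outcome definition, so that cannot be shown. A random-timing model, in which one episode a year falls in a given month with probability 1 − exp(−1/12) = 8%, describes a single component with an assumed frequency, not the four-part outcome. A reader might also infer that [8] is the wrong reference. Without sight of [8] one can say only that the two sections do not match.

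These points limit the size of the fault. They do not supply a justification for the 95%, which is still argued from behaviour alone.

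**Conclusion.** The point holds in a limited form and is a should-fix. The 95% control rate is unsupported for the outcome as defined, and the true rate is likely to be lower by an unknown amount. The 90% power is therefore conditional, although the plan states it without that condition. A control rate only 5 points lower takes power below 90% across the planned 200 to 250 men; further falls cost more, especially if the treatment effect is relative rather than absolute. These results rest on assumed control rates, on men who decline MI behaving like controls, and on equal 20% loss. The sample-size arithmetic is correct, and the validity of the primary comparison is not affected by this point.

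**What to change.** 1. State in the Sample size section that 90% power holds only if 95% of controls meet the 3-month outcome definition.
2. Replace the single figure with a table of power over control rates of, say, 60–95% and differences of 10–20 points, labelled as assumptions, at 80 to 100 evaluable per arm.
3. Where the baseline items allow, score the self-reports of eligible men with the 3-month definition as they accrue. The Outcome measures section indicates that the same tools are used at baseline but does not show that month and week windows were asked. Re-interviews run over 18 months, so this cannot set the sample size beforehand; it can inform the expected control rate and the reading of a null result.
4. Reconcile the citation of [8] for the difference with the Background section's use of [8] for volume and [9] for proportions.

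The cost is some rewording, one tabulation of baseline data and a less favourable stated power. Correcting the statement needs no extra men.

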### Type of analysis

The primary analysis will be based on a difference in the number of men classified as hazardous drinkers at the 3 month assessment between the randomised groups using the intention to treat principle. This may dilute the treatment effect but the analysis will not be biased if the loss to follow up, especially for the primary outcome is similar between the two randomised groups.

Differential effects by subgroup analyses based on important prognostic factors such as age group and severity of alcohol dependence will be assessed using interaction tests. We are aware that in this exploratory trial the results of such analyses will only be indicative.

In addition, the availability of the baseline information on all participants in the Izhevsk family study II will enable us to assess the extent to which those people included in the trial differ systematically from the population sample from which they were drawn, and will provide external validation for any trial findings.

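### The lower part of the 200 to 250 range falls slightly short of 90% power under intention to treat if men who refuse MI drink like controls: 228 men are then needed, and 200 give about 86%

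*Protocol article*

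**What the plan says.** The Sample size section takes hazardous drinking at 3 months as 95% in the control arm and 75% in the intervention arm, to be detected "with 90% power at the 5% level of statistical significance". From this it concludes: "A sample of at least 130 men (65 in each arm) will therefore be required".

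Two allowances follow. For refusal, because men are randomised before they consent to MI, "we assume that 20% of the participants in the intervention arm will not agree to receive the intervention". For attrition, "We also assume that there will be a 20% loss to follow for the 3 month assessment in both trial arms". The result is "This requires inflating the sample size to between 200 and 250 participants". The section names no single target within this range, gives no power for either end and does not show the inflation step.

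The Type of analysis section makes the primary comparison between the groups as randomised, by intention to treat, and says of this: "This may dilute the treatment effect".

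**The concern.** Loss to follow-up and refusal of MI act differently in an intention-to-treat analysis. A man lost at 3 months has no outcome, so loss reduces the number analysed. A man who refuses MI but is followed up is still counted in the intervention arm, so refusal leaves the number unchanged and reduces the difference between the arms. The required sample size rises roughly with the inverse square of that difference, so refusal costs more than the same percentage of loss.

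The plan counts both allowances into one rounded range. If refusal is handled as dilution, the lower part of the range may not deliver the stated 90% power, and a reader cannot tell, because no power is attached to either end. The section also says that one aim of the trial is to test these assumptions for a later definitive study, so the way refusal enters the calculation should be visible.

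**Working it through.** **Inputs from the Sample size section:** control rate 95%; intervention rate 75%; power 90%; 5% level (sidedness not stated; two-sided reproduces the plan's figure, one-sided gives 53 per arm); refusal 20% in the intervention arm; loss 20% in both arms. **From Type of analysis:** intention to treat.

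**Inputs the plan does not state (assumptions):** (a) refusers drink hazardously at the control rate of 95%; (b) loss is unrelated to refusal.

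**Step 1: reproduce 65 per arm.** Two-sided test of two proportions, pooled variance under the null, no continuity correction:

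n = [1.960·√(2p̄(1−p̄)) + 1.282·√(p₁(1−p₁) + p₂(1−p₂))]² / (p₁−p₂)²

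With p₁ = 0.95, p₂ = 0.75, p̄ = 0.85: n = (0.990 + 0.621)² / 0.20² = 64.9, so 65 per arm and 130 in total. This matches the plan, and the same formula is used below.

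**Step 2: dilute for refusal.** Intervention arm under intention to treat: 0.8 × 75% + 0.2 × 95% = 79%. The difference falls from 20 to 16 points.

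**Step 3: sample size for 95% v 79%.** With p̄ = 0.87: n = (0.932 + 0.592)² / 0.16² = 90.7, so 91 evaluable per arm. After 20% loss: 91 / 0.8 = 113.75, so 114 per arm and **228 randomised**.

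**Step 4: power across the stated range**, with evaluable men per arm = 0.8 × N / 2:

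| Randomised | Evaluable per arm | Power, same formula | Exact, uncorrected chi-square | Exact, Fisher |
|---|---|---|---|---|
| 200 | 80 | 86.0% | 88.3% | 83.6% |
| 228 | about 91 | 90.1% | 92.2% | 88.0% |
| 250 | 100 | 92.6% | 94.4% | 91.5% |

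Other sample-size formulas for 95% v 79% with 20% loss need about 209 (arcsine), 220 (unpooled variance) or 258 (continuity-corrected) men. All exceed 200.

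**Step 5: sensitivity to the unstated assumptions, at 200 randomised (80 evaluable per arm).**
- Refusers at 90%: intervention arm 0.8 × 75% + 0.2 × 90% = 78%; power 89.0%.
- Refusers at 85%: intervention arm 77%; power 91.4%.
- Refusers at 95%, but half of them among those lost: of 100 men, 20 refuse and 20 are lost, 10 of the latter being refusers. That leaves 70 accepters and 10 refusers, so (70 × 75% + 10 × 95%) / 80 = 77.5%; power 90.3%.

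**Possible origin of the range (inference only).** 130 / (0.8 × 0.8) = 203 is close to the lower end and would treat refusal as lost headcount. 130 / (0.8² × 0.8) = 254 is close to the upper end and would treat refusal as dilution.

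**The case against.** The strongest reply is that 228 lies inside the stated range, close to its midpoint, and that 250 gives more than 90%. That is right: the range as a whole is not wrong, and no printed figure is miscalculated. Only the part below about 228 falls short.

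A second reply is that the 79% is not the plan's own number. This also stands in part. Men in the intervention arm are told about the trial when consent is sought (Randomisation and consent), while controls are not, and the Ethics and confidentiality section says that such knowledge can change drinking substantially. Refusers might therefore do better than controls, and refusal and loss might overlap. Step 5 shows that modest departures of this kind remove most or all of the gap. Against this, the Sample size section considers a spontaneous reduction beyond 5% unlikely, so 95% is the plan's own figure for untreated men and the natural default.

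A third reply is that the 20-point difference is already the intention-to-treat difference. Then 130 / 0.8 = 162.5, about 163 men, would suffice, and 200 would give 95%. But the section gives refusal as a separate reason for inflating, which does not fit that reading.

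Finally, the trial is exploratory, and its assumed effect is described as near the upper limit of what earlier work projects. That uncertainty is larger than the gap between 200 and 228, which limits the weight of the point without removing it.

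**Conclusion.** The point holds in a limited form, and its severity is minor. If refusers stay at 95% and loss is unrelated to refusal, 200 randomised men give 86% power, a type II error of 14% instead of 10%, and 228 are needed for 90%. With exact calculation the figure at 200 is 88% (uncorrected chi-square) or 84% (Fisher); the article does not name the test.

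A reader might infer more than the document supports:
- **That the trial as planned is underpowered.** It is not, on these figures, anywhere from 228 to 250.
- **That the shortfall follows from the plan's assumptions alone.** It needs the two unstated inputs above.
- **That the lower limit came from counting refusers as lost men.** The match with 203 is a possible explanation, but the article does not show the step.
- **That recruitment is meant to stop at 200.** Nothing says so. The range simply leaves the target open.

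**What to change.** In the Sample size section, state the diluted contrast and its assumptions, and attach power to the range. For example: *Assuming that men who refuse MI remain at the control rate of 95% and that loss to follow-up is independent of refusal, the intention-to-treat contrast is 95% v 79%; this requires 91 evaluable men per arm, or 228 randomised. With 20% loss, 200 men give about 86% power and 250 give about 93%.* Then either keep the range with these powers, or make 228 its lower limit.

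The cost is one or two sentences, with no change to design, outcome or analysis. The figure of 228 is below the 300 eligible men expected in the Recruitment rate section (2000 × 60% × 25%), although men who decline the health check or follow-up are excluded and will reduce that pool.
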